### Follow up procedures

We propose testing the feasibility of using a follow up method that is unlikely to be perceived by participants as providing them with behavioural support or enhance motivation to adhere. This will be by email/Webform emailed monthly for the 12 months of a participant's involvement in the trial. Monthly follow up will ensure that we can assess whether smokers have started their period of abstinence and schedule verification visits, based on a process outlined for trials of this kind [18]. Web follow up has achieved > 90% follow up in a previous trial [19]. Based on our experience of trials in smokers' clinics, most patients have email addresses and these are useful for follow up. Text reminders will be sent to participants registered for email follow up not responding to the email. For those not using a computer regularly, phone follow up by telephonists will be used so that the pharmacist/therapist is not conducting follow up.

Sustained smoking reduction will be measured as self-reported daily cigarette consumption at 12 month follow up, with a reduction being counted as self-reported consumption lower than at baseline. Sustained reduction will be counted as achieved if during the last four months (i.e. reports at month 9-12) of follow up, a person is smoking less at every follow up occasion than at baseline, measured by self-report. If a monthly report is missing, a person will be counted as having achieved sustained reduction if all other reports show this is the case and the last report is not missing. If two reports are missing, a person will be counted as not having achieved sustained reduction. Mean cigarettes per day at the end of follow up will be calculated from the last follow up only. If cigarettes per day is missing, then this will be replaced by baseline cigarettes per day, but in sensitivity analysis, we will use last observation carried forward.

Participants who have maintained abstinence for 4 weeks will be asked to attend the pharmacy for carbon monoxide (CO) verification if they are in the self-help arm or if they are in the supported arm but are not due for or have ceased to attend visits. Those who have maintained abstinence for 6 months (defined in the same way with a grace period and no more than five cigarettes smoked) will be asked to return for CO verification in the same way. Participants attending the pharmacy for a non-therapeutic reason i.e. to attend for abstinence verification will be paid £20 to compensate them for their time and any travel costs incurred.

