**Design and methods:**

This is a 2 × 2 randomised factorial trial of behavioural support versus no support and short versus standard length reduction programme. The pharmacists will recruit 16 patients per pharmacy, 160 smokers altogether. Pharmacists will randomise each participant by sealed envelopes. In a standard supported programme, the pharmacist will give support for 34 weeks, inviting participants to set a treatment goal and providing advice on how to reduce cigarette use. Participants in the short programme will be given the same advice on how to reduce but will reduce smoking over four weeks. Participants in the no support arms will be given a leaflet that describes the reduction programmes in 4-week and 34-week format. All participants are encouraged to use of NRT to support the reduction. These processes will be measured by recording the number of recruited smokers; percentage of those who reduce and sustain their consumption to at least 50% of baseline value, and the proportion of people who attain 4 weeks abstinence and 6 months abstinence. Interviews will assess smokers' and pharmacists' views on the way the programme ran.

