### Trial Outcomes

This is a pilot trial designed to test the processes, examine implementation issues, and reactions to the programme of those involved i.e. whether pharmacists can be trained to implement the reduction programme, how well they do so, and how this is received by smokers and by pharmacists. These processes will be measured by:

• The percentage of pharmacists that agree to participate and the percentage that are trained and pass an assessment of competence.

• The monthly recruitment rate of patients into reduction programmes and into NHS stop smoking programmes, comparing the rate of recruitment into stop smoking programmes for pharmacists participating in the trial with those not doing so.

• Recording of some consultations and analysing their content against the schedule of proposed content.

• The proportion of people that would recommend the smoking reduction programme to another smoker and their views on the way that it ran, taken from the 12 month evaluation questionnaire.

We will also examine whether behavioural support is more effective than no support and will investigate whether shorter reduction programmes are more effective than standard length reduction programmes. This will be achieved by measuring self-reported sustained smoking reduction and abstinence. Smoking cessation outcomes will be measured from the time of quitting and we will measure 4 week and 6 month prolonged abstinence following the Russell standard, i.e. by intention to treat and biochemically confirmed [12]. Thus abstinence will be defined as allowing a two week grace period after quit day in which smoking lapses do not count against abstinence and from day 15 onwards, no more than five cigarettes have been smoked. This will be verified by a CO < 10 ppm. Smoking reduction will be assessed by the proportion of people that reduce their consumption to < 50% of baseline value, the mean cigarette consumption at the end of the trial.

As this is a preliminary trial, we will record data to allow us to assess whether the processes of the trial need improvement prior to a definitive trial. We will also examine data on adverse events and drop outs from the programme (Appendix 1).

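### Smoking reduction is defined in contradictory ways, and the only scoring rule for sustained reduction counts any fall below baseline rather than the 50% threshold stated elsewhere

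*Protocol article*

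**What the plan says.** The protocol article defines smoking reduction in three places.

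- **Abstract, Design and methods:** the outcome is the "percentage of those who reduce and sustain their consumption to at least 50% of baseline value". No window is given.
- **Trial Outcomes:** reduction is assessed by "the proportion of people that reduce their consumption to < 50% of baseline value", again with no window. The same section rests the reduction outcome on self-report: "This will be achieved by measuring self-reported sustained smoking reduction and abstinence".
- **Follow up procedures:** sustained reduction is first described as daily consumption reported at 12 months, "with a reduction being counted as self-reported consumption lower than at baseline". A second sentence sets the test on the four monthly reports from month 9 to month 12, and requires that "a person is smoking less at every follow up occasion than at baseline, measured by self-report". One missing report is tolerated if "all other reports show this is the case and the last report is not missing". Beyond that, "If two reports are missing, a person will be counted as not having achieved sustained reduction".

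Follow up procedures sets no minimum size of fall and does not mention 50%. Primary objectives 2 and 3 compare programmes on reduction as well as cessation. Secondary objective 2 is the proportion of enrolled smokers who reduce successfully. The Statistics section commits to an intention-to-treat analysis of reduction.

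**The concern.** One named outcome has two thresholds, and the more lenient one is attached to the only rule detailed enough to program. Two analysts working from different sections would report different proportions for the same participants, and the choice could be made after the data are seen.

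The Abstract's wording adds to the problem. Reducing to at least half of baseline means still smoking half or more of it, so a participant who cut down further would fail.

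The lenient rule also gives little protection against noise. The outcome is self-reported, and one cigarette fewer than baseline at each report is enough. Some smokers whose habit has not changed would be scored as sustained reducers, and the reported percentage would not be the 50% outcome that the Abstract announces.

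**Working it through.** The article states no misclassification rate or power for the reduction outcome, so there is no plan figure to reproduce.

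**1. The definitions side by side.** Take a baseline of 20 a day, so half is 10. Trial Outcomes gives no window; month 12 is used here for the comparison.

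| Reports at months 9, 10, 11, 12 | Follow up procedures, every report | Trial Outcomes, at month 12 | Abstract, taken literally | Abstract, read as a fall of at least half |
|---|---|---|---|---|
| 19, 19, 19, 19 | yes | no | yes (95% of baseline) | no |
| 10, 10, 10, 10 | yes | no (not below 10) | yes (50%) | yes |
| 8, 8, 8, 8 | yes | yes | no (40%) | yes |
| 20, 8, 8, 8 | no | yes | no (40% at month 12) | depends on the missing window |

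The disagreement runs in both directions, and no two columns agree on every row.

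**2. Chance success under Follow up procedures.** The inputs from the document are one baseline value, four follow-up reports, a strict inequality and the missing-report rule. Everything about variability below is assumed.

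*Exchangeable reports without ties.* An unchanged smoker succeeds if baseline is the highest of five values: 1/5 = 20%. With one non-final report missing, it need only be the highest of four: 1/4 = 25%.

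*Reports missing at random with probability q.* Success needs either no report missing, or one of the first three missing:
(1 - q)^4 × 1/5 + 3q(1 - q)^3 × 1/4.
- q = 0.05: 0.1629 + 0.0322 = 19.5%
- q = 0.10: 0.1312 + 0.0547 = 18.6%
- q = 0.20: 0.0819 + 0.0768 = 15.9%

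Across a whole arm, missing reports therefore lower the rate, although the tolerance for one missing report raises it for the people it covers.

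*Repeated answers.* A tie with baseline is not a reduction. If each report repeats the baseline number with probability u, the rate is (1 - u)^4 × 1/5: 8.2% at u = 0.2, 2.6% at 0.4 and 0.5% at 0.6.

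*Simulation of unchanged smokers.* The main set had 1,000,000 per scenario, mean 20 a day and within-person SD 1 to 5. The second set had mean 18, between-person SD 7, baseline at least 10 a day and within-person SD 2 to 4.

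| Reporting pattern | Scored as sustained reducers |
|---|---|
| Whole numbers, main set | 11.1-17.8% |
| Nearest five, main set | 0.6-11.2% |
| Continuous, second set | 22-23% |
| Whole numbers, second set | 16-19% |
| Nearest five, second set | about 6-10% |
| Continuous, follow-up reports serially correlated 0.3-0.9 | 23-39% |
| Continuous, baseline at least 10 a day, true mean 11 to 15, SD 3 | 31% down to 21% |

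**3. The 12-month sentence read alone.** With two exchangeable, tie-free reports the chance of a lower second value is 1/2. For whole numbers in the main set it is 36-47%. The window therefore matters as well as the threshold.

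**4. The same smokers under a below-50% rule.** Required at all four reports, with rounding to whole numbers or fives in the main set, at most 0.07% qualify. At month 12 alone the figure is 0-5%.

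**5. Effect on the reported result.** Suppose a share f of non-reducers is scored as reducers in every arm and all true reducers are counted. An arm with true proportion p then reports p + f(1 - p), and a difference between arms is multiplied by (1 - f). With f = 0.20 the difference keeps 80% of its size. The rate rises in every arm and the contrast shrinks towards zero.

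**The case against.** The best defence is that Trial Outcomes gives the size of a reduction and Follow up procedures its persistence, so the two are separate descriptors. This would be tenable if those were the only sections. It fails because the Abstract joins sustaining to a 50% threshold, while Follow up procedures defines sustained reduction with no threshold.

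The second defence concerns weight, and it stands. This is a pilot. The Sample size section makes four-week abstinence the main efficacy outcome, and no sample size rests on reduction. The planned analysis is largely descriptive, mean cigarettes per day needs no threshold, and the monthly counts allow either definition to be computed.

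Three stronger readings are tempting and are not supported:

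- A reader might infer that one in five unchanged smokers will be scored as sustained reducers. That figure needs five exchangeable reports that never tie. Cigarettes per day is a count, often open to rounding, and ties count as failure. The article gives no within-person variability and does not say how baseline consumption is obtained.
- A reader might infer that entry at 10 or more a day guarantees regression to the mean. The Inclusion criteria also admit people by a CO reading, so consumption is not a floor for everyone.
- A reader might infer bias towards one arm, since the trial is open label. The rule itself treats all arms alike, and nothing in the document quantifies differential reporting.

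**Conclusion.** The contradiction holds on the text alone. The three sections classify the same participant differently, and the one operational rule accepts a one-cigarette or chance fall as sustained reduction. The 12-month and month 9-12 descriptions also need reconciling.

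The numerical size is illustrative. The 20% figure is the exchangeable, tie-free case, and the span of under 1% to about 39% reflects assumptions about rounding, repetition, serial correlation and selection, none of which the document settles. What is stable is the contrast with a sustained below-50% rule, under which chance success is about 0.1% or less in the scenarios run.

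The consequence is a higher reduction rate in all arms and a result that is not the announced 50% outcome. This should be fixed before the reduction outcome is analysed. It does not undermine the pilot or its abstinence outcomes.

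**What to change.** Use one definition in the Abstract, Trial Outcomes and Follow up procedures: self-reported consumption below 50% of baseline at every available report from months 9 to 12. Keep the strict inequality of Trial Outcomes, so that a person at exactly half of baseline is scored the same way everywhere. Keep the existing missing-report rule.

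Reword the Abstract so that it describes smoking less than half of baseline. Remove the sentence that describes sustained reduction as consumption at 12 months, or label that quantity separately. Report any reduction below baseline only as a labelled secondary description.

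The cost is wording: the monthly reports are already planned. The headline reduction rate will be lower than under the present rule.

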Any trial to test the role of behavioural support and shorter versus standard length reduction programmes would need to use six month prolonged smoking abstinence as the outcome [11,12]. A sample of 160 participants is not large enough to provide definitive evidence of efficacy with such an outcome because our systematic review showed that standard length programmes lead to about 7% of participants sustaining six month abstinence [13]. However, we assume that shorter reduction programmes are about twice as effective, as suggested by the Haustein trial. Our most important efficacy outcome here is four week abstinence. Based on our systematic review, we expect about 7% of participants who follow the standard length programme with behavioural support to sustain abstinence for six months, which equates to about 21% achieving 4 weeks of abstinence, our main efficacy outcome. Based on this, we get the following table, which shows that this sample size will have 80% power to detect a rate ratio of 1.7 or 90% power to detect a rate ratio of 1.8 (Table 1), lower than observed in Haustein.

**Table 1 T1:** Efficacy of shorter reduction programmes versus standard length

			80% power	90% power
**Base quit proportion**	**RR**	**Quit proportion in intervention**	**N in each arm**	**N in each arm**

0.21	1.7	0.357	146	195

0.21	1.8	0.378	114	152

0.21	1.9	0.399	91	122

The following are also considerations in the sample size. If we take key process measures like attendance for behavioural support sessions as 63% (observed in the review), with 80 smokers receiving behavioural support, we could estimate this with +/-7% precision with 80% confidence. Asking each pharmacy to treat 16 patients, 4 in each arm, will give a reasonable range of experiences for them and us to evaluate the programmes.

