**Figure 1 F1:**
[figure not shown]
**Randomised factorial design trial (2 × 2) of behavioural support versus no support on smoking reduction**.

All participants will receive NRT and be randomised to either behavioural support or no support and either standard length or short reduction; approximately 80 people in each arm.

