### No support arms

Participants in the no support arms will not be given advice or support by the pharmacist. Instead they will be given a leaflet that describes the reduction programmes (unstructured, cigarettes per day, or smoking periods) and which gives brief advice on using one or more of these approaches, and encourages use of NRT to support this. Participants will be advised to reduce on a schedule that follows the standard programme, if randomised to that arm, or the short programme, if randomised to that arm. The leaflet will advise participants to return to the pharmacy for more NRT to support reduction as needed. This will be dispensed on NHS prescription (following the primary care trust's patient group direction). The outcomes will be monitored without personal visits to avoid the possibility that these are contributing to adherence to the programme.

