### Transferring to the cessation programme

The aim of the reduction programme is to help people reduce and pharmacists will be encouraged not to pressure people to stop smoking, while explaining that proven health benefits derive from smoking cessation rather than reduction. However, most people who want to reduce smoking want to do so as a way of stopping [16,17], though rarely with a predetermined timetable. It is for the therapist and the patient to determine whether and when a person is transferred to the cessation programme. Pointers towards possible cessation are:

• Increased confidence that the patient can control her/his smoking.

• Cigarette consumption has fallen to five per day or fewer, or the person is going most of the day without smoking.

Participants in the No-support arms will be asked about their quitting attempt when they return to the pharmacy for more NRT. A key principle of the whole reduction approach is that failed quit attempts do not lead to an end of the programme. If a person moves to cessation and the quit attempts fails, they can resume the reduction programme and continue to control their smoking until they are ready to stop again.

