### Data analyses

#### Statistics

We will calculate descriptive statistics for the outcome measures comparing these by arm where it is sensible to do so. Risk differences with 95% confidence intervals will be calculated for binary outcomes such as cessation, and for continuous outcomes, such as reduction in cigarettes per day, we will calculate difference in means or difference in change in means. For the cessation and reduction outcomes, we will conduct an intention-to-treat analysis, where all randomized subjects will be included in the denominator. We will also conduct sensitivity analyses with different assumptions for missing data.

The data will be analysed by a multilevel model by examining diversion of smokers from cessation into reduction programmes by comparing uptake of cessation in the pharmacies prior to and during the reduction programmes with pharmacies providing a similar throughput of patients for cessation support but not selected to provide reduction programmes.

Health economic analyses are not required because extensive modelling of different formats of reduction programmes showed that each of these programmes are cost-effective by NHS standards and this was robust to changes in assumptions [3]. However, we will utilise our existing models of the cost-effectiveness of the programme by updating the estimates used in modelling by including these estimates derived from a naturalistic setting. The updated estimates will be used to set the sample size for a definitive trial.

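### The route to CO verification depends on support allocation, which puts the support versus no-support comparison of four-week abstinence at risk of differential ascertainment

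*Protocol article*

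**What the plan says.** All references are to the Protocol article.

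- **Follow up procedures, verification.** Participants who have kept four weeks of abstinence are "asked to attend the pharmacy for carbon monoxide (CO) verification if they are in the self-help arm". Those in a supported arm are asked to come specially only when no support visit is due or they no longer attend. The same rule applies at six months.
- **Follow up procedures, payment.** "Participants attending the pharmacy for a non-therapeutic reason i.e. to attend for abstinence verification will be paid £20".
- **Follow up procedures, detection.** Abstinence is picked up, and verification visits scheduled, through monthly email, webform or telephone contact. This is described without distinction by arm.
- **Trial Outcomes and Statistics.** Abstinence follows the Russell standard, by intention to treat and with biochemical confirmation (CO below 10 ppm). All randomised participants are in the denominator. "Risk differences with 95% confidence intervals will be calculated for binary outcomes such as cessation". Sensitivity analyses for missing data are planned in general terms.
- **Sample size.** The expected rate for the supported standard programme is 7% at six months, "which equates to about 21% achieving 4 weeks of abstinence, our main efficacy outcome".
- **Transferring to the cessation programme.** "Participants in the No-support arms will be asked about their quitting attempt when they return to the pharmacy for more NRT".
- **No support arms.** "The outcomes will be monitored without personal visits to avoid the possibility that these are contributing to adherence to the programme".

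**The concern.** A self-help abstainer can be confirmed only by making a separate trip to the pharmacy. A supported abstainer may be confirmed at a visit already in the diary. The effort needed to become a confirmed abstainer therefore depends on the randomised factor under comparison.

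The protocol does not state in so many words that an unverified claim counts as smoking. Required biochemical confirmation with a full denominator leaves no other evident reading, so any difference between arms in attendance for testing becomes a difference in the outcome.

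The comparison affected is primary objective 3 (supported versus self-guided programmes), on the outcome the protocol calls its main efficacy outcome. The Statistics section intends to use updated estimates from this trial to set the size of a definitive one, so an artefact could carry forward. Because the rule governs how data are collected, a later analysis plan cannot fully repair it.

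The protocol is also at odds with itself. It says that outcomes in the no-support arms are monitored without personal visits, yet it requires a personal visit in those arms to confirm the main efficacy outcome.

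**Working it through.** **Plan's own figures.** The concern rests on no stated figure. Table 1 was reproduced only to confirm the inputs. A two-sided 5% test of two proportions from a base of 0.21, with pooled variance and no continuity correction, gives 147/196, 115/153 and 92/123 per arm. The table states 146/195, 114/152 and 91/122, each within one. The two-sided 5% level is inferred from the planned 95% intervals.

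**Inputs.**
- True four-week abstinence p = 0.21 (Sample size). The protocol gives this for the supported standard programme. Applying it to both levels of the support factor is an assumption, made so that the true effect is nil.
- n = 80 per level of the factor (Figure 1 legend: "approximately 80 people in each arm").
- Probability that a true abstainer is CO-verified: v_s (supported) and v_n (self-help). The protocol gives neither, so both are assumed and varied.

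**Formulas.** Observed rate = p × v. False rate ratio = (p × v_s)/(p × v_n) = v_s/v_n, whatever p is. False risk difference = p × (v_s − v_n).

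| v_s | v_n | False RR | False risk difference at p = 0.21 | People of 80 |
|---|---|---|---|---|
| 90% | 90% | 1.00 | 0 | 0 |
| 95% | 85% | 0.95/0.85 = 1.12 | 0.21 × 0.10 = 2.1 points | 1.7 |
| 95% | 75% | 0.95/0.75 = 1.27 | 0.21 × 0.20 = 4.2 points | 3.4 |
| 70% | 90% | 0.70/0.90 = 0.78 | 0.21 × (−0.20) = −4.2 points | −3.4 |

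**Scale.** The Background cites a 50 to 100% gain from behavioural support in cessation programmes. A false RR of 1.27 is about half the lower end of that gain (0.27/0.50 = 0.54). Against sampling error it is modest: with 21% in both groups of 80, the 95% half-width for the risk difference is 1.96 × √(2 × 0.21 × 0.79/80) = 12.6 points.

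**Does one supported arm gain more?** Visits in the standard programme are at weeks 2, 6, 10, 16, 22, 28 and 34 after baseline. A quit at week 2 meets the week 6 visit four weeks later, and a quit at week 6 meets week 10. In the short programme a quit at week 4 meets week 8, but its fallback quit at week 8 has no visit until week 16. Both schedules offer some matches, so only the contrast of support with no support is at issue.

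**Six months.** Taking six months as 26 weeks, and counting only the reduction-programme visits, the short programme's last visit (week 16) comes too early to verify anyone. In the standard programme the last visit is week 34, so only participants who quit by week 34 − 26 = 8 could be verified at a support visit. Most supported abstainers would then need the same paid special visit as self-help abstainers.

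**The case against.** The strongest reply is that much of the procedure is already common to all arms.

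- **Trigger.** A reader might infer that detection of abstinence differs by arm. It does not: the monthly remote contact is described for everyone. Only the step from report to CO test differs. This objection stands.
- **Payment.** A reader might infer that the £20 is paid by arm. It follows the type of visit, and a supported participant who comes only for verification falls under the same payment. This stands, although visit type itself depends partly on arm: every self-help verification is a special visit, and only some supported ones are.
- **Direction.** The extra trip could lower confirmation in the self-help arms, while the special invitation and £20 could raise it. Supported abstainers between visits face the same trip. This stands, so a bias in favour of support cannot be asserted.
- **Pharmacist's enquiry.** A reader might take the question about quitting at NRT collection as outcome collection that breaks the no-visit principle. It belongs to the section on transfer to cessation and adds no visit. The firmer conflict is between the no-visit statement and the CO visits.
- **Pilot status.** The protocol says the trial is not powered for differences in abstinence, is testing its follow-up method, and plans missing-data sensitivity analyses. This limits the consequence. But the effect estimates are meant to inform a definitive trial, improving trial processes is a stated purpose of the pilot, and no sensitivity analysis is stated for unverified self-report.

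**Conclusion.** The concern holds as a risk of differential ascertainment in the four-week abstinence comparison of support with no support. The protocol fixes a verification route that differs by randomised support status, and its outcome definition turns missed verification into failure.

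It would be going too far to say that the comparison is biased, that it favours support, or that the supported short arm gains most. The documents give no verification rates, and the visit schedules do not single out one supported arm.

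Under assumed verification gaps of 10 to 20 points either way, the distortion is about 2 to 4 percentage points, or two to three people in 80. The corresponding false RR runs from 0.78 (70% v 90%) to 1.27 (95% v 75%). With equal verification there is none. The issue bears mainly on four weeks and should shrink at six months. It is worth correcting because the remedy is cheap and has to be in place when the data are collected.

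**What to change.** 1. In Follow up procedures, use one verification procedure in all four arms. The existing monthly report is the only trigger. The window after it, the type of verification attendance and the £20 payment are the same for everyone. Readings taken at routine support visits do not count as verification.
2. Report attendance for verification by arm, as a proportion of those who reported qualifying abstinence. Add a sensitivity analysis on self-reported prolonged abstinence.
3. Reconcile the statement under No support arms that outcomes are monitored without personal visits with the CO visits under Follow up procedures and with the pharmacist's enquiry under Transferring to the cessation programme. Whether that enquiry is kept is for the investigators to decide.

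**Cost.** Some supported abstainers make an extra attendance. Additional payments at four weeks are at most about 80 × 0.21 = 17 to 80 × 0.357 = 29, or £340 to £580, using the base rate and the RR 1.7 rate in Table 1. This is an upper figure at those rates, because supported participants attending only for verification are already paid. Some further payments would arise at six months.
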